## Abstract

**Background:**

Negative affective states such as anxiety, depression and stress are significant risk factors for cardiovascular disease, particularly in cardiac and post-cardiac rehabilitation populations.

Yoga is a balanced practice of physical exercise, breathing control and meditation that can reduce psychosocial symptoms as well as improve cardiovascular and cognitive function. It has the potential to positively affect multiple disease pathways and may prove to be a practical adjunct to cardiac rehabilitation in further reducing cardiac risk factors as well as improving self-efficacy and post-cardiac rehabilitation adherence to healthy lifestyle behaviours.

**Method and design:**

This is a parallel arm, multi-centre, randomised controlled trial that will assess the outcomes of post- phase 2 cardiac rehabilitation patients assigned to a yoga intervention in comparison to a no-treatment wait-list control group. Participants randomised to the yoga group will engage in a 12 week yoga program comprising of two group based sessions and one self-administered home session each week. Group based sessions will be led by an experienced yoga instructor. This will involve teaching beginner students a hatha yoga sequence that incorporates asana (poses and postures), pranayama (breathing control) and meditation. The primary outcomes of this study are negative affective states of anxiety, depression and stress assessed using the Depression Anxiety Stress Scale. Secondary outcomes include measures of quality of life, and cardiovascular and cognitive function. The cardiovascular outcomes will include blood pressure, heart rate, heart rate variability, pulse wave velocity, carotid intima media thickness measurements, lipid/glucose profiles and C-reactive protein assays. Assessments will be conducted prior to (week 0), mid-way through (week 6) and following the intervention period (week 12) as well as at a four week follow-up (week 16).

**Discussion:**

This study will determine the effect of yoga practice on negative affective states, cardiovascular and cognitive function in post-phase 2 cardiac rehabilitation patients. The findings may provide evidence to incorporate yoga into standardised cardiac rehabilitation programs as a practical adjunct to improve the management of psychosocial symptoms associated with cardiovascular events in addition to improving patients’ cognitive and cardiovascular functions.

**Trial Registration:**

ACTRN12612000358842

## Background

Cardiovascular disease (CVD) is a leading cause of morbidity and mortality worldwide. In 2004, CVD caused 17.1 million deaths and this is estimated to increase to 23.6 million by 2030 [1]. This increase is paralleled by an increase in the prevalence of psychological risk factors such as anxiety, depression, and stress that have been shown to be associated with CVD morbidity and mortality [2, 3]. Anxiety and depression are common after CVD events with prevalence rates up to 31%. Interestingly, anxiety and depression in CVD patients appear to be independent of functional health, time between cardiac incidents, and enrolment in cardiac rehabilitation (CR) programs [4–6]. Furthermore, these psychosocial factors often cluster within an individual with a significant number of patients presenting with multiple psychological symptoms upon CR entry [5]. This evidence is particularly concerning as these affective symptoms have been shown to increase the risk of primary and subsequent cardiovascular events, and contribute to poor behavioural aspects that affect general cardiovascular health [7–9]. While anxiety and depression are distinctly separate at a conceptual level, past attempts to quantify these constructs yielded high degrees of inter-correlation [10]. This has resulted in the development of a tripartite continuum with anxiety and depression at opposite extremes and a centralised nonspecific component, which encompasses key aspects of stress [11].

Numerous studies have demonstrated that psychosocial stress is a significant risk factor for CVD in both patients with established disease and healthy individuals [7, 12] and large scale community-based studies as well as prospective studies have found significant relationships and prevalence rates between anxiety, depression and CVD risk [13–15]. Whilst the precise physiological and biochemical mechanisms that underlie the bidirectional associations between these negative affective states and CVD are not well understood, a number of studies have implicated hypothalamic-pituitary-adrenal axis dysfunction, activation of pro-inflammatory cytokines, autonomic dysregulation and increased markers of inflammation as possible key neurobiological mechanisms [16–18]. In addition to this, previous evidence indicates negative behavioural patterns in patients with high anxiety or depression such as less contact with their cardiologists, being less likely to seek preventative medical care, poorer medication compliance as well as reduced self-motivational, and physical inactivity that further worsens cardiac outcomes [5, 19]. Furthermore, patients with anxiety or depression, even at subclinical levels exhibit significantly lower quality of life (QoL) scores [5, 20].

In an attempt to reduce the prevalence and progression of CVD, cardiac rehabilitation and prevention programs which incorporate exercise regimens, stress management techniques and patient education, have gained widespread acceptance and have been shown to improve risk factor management and functional capacity thereby reducing the chance of secondary cardiovascular incidences [21]. CR programs have also been shown to improve cognitive function, QoL, and psychosocial outcomes and programs with an exercise component also have benefits on mortality. However in spite of these benefits, CR programs remain underutilised with only an estimated 30% of eligible patients in Australia participating [22, 23]. Whilst it is widely believed that continued exercise and physical activity is required to sustain most of the benefits gained through the participation of CR, studies have reported an adherence rate to physical activity of 30% to 60% in those who complete phase 2 rehabilitation programs [24, 25]. This has been highlighted in a study of myocardial infarction (MI) patients where CR benefits diminished to a level in which no significant differences between CR and non-CR participants could be seen 6 months post-MI [26]. Therefore, a practical adjunct which can improve physiological and psychosocial risk factors may further reduce cardiac risk factors and improve self-efficacy and long-term adherence to healthy behaviours.

Yoga may be one such treatment [27]. It is described as a path, which integrates the body, senses, mind, and intelligence with the self and numerous studies have reported the benefits of yoga in reducing stress, anxiety, and depressive symptoms in healthy and psychologically affected volunteers [28–30]. This is consistent with numerous reviews that highlight the positive potential of yoga for the treatment of depressive and anxiety disorders [31–34]. Whilst the methodological quality of prior yoga studies are generally weak, there are multiple reviews that highlight the favourable effects of yoga in improving the cardiovascular profile across a range of clinical and healthy populations [35–37]. Significant improvements in a wide range of cardiovascular parameters such as the high frequency component of heart rate variability (HRV), pulse wave velocity (PWV), blood lipid profiles (low density / high density lipoproteins and triglycerides), and C-reactive proteins (CRP) highlights the broad range of effect yoga has on the cardiovascular system [37–45]. Hatha yoga is consider to achieve benefits in blood circulation by enhance the effect of circulatory pumps in the body. Dynamic exercises such as *vinyasas* focus on activating and relaxing muscles during movement to enhance the effects of the musculoskeletal pump. Furthermore co-activation of antagonistic muscles during *vinayasas* and static postures (*asanas*) can create regions of relatively low and high pressures to augment muscle co-activation and postural circulation pumps to improve blood circulation [46].

To complement the array of psychosocial and cardiovascular impact of yoga, recent studies linking the detrimental effects of CVD and arterial stiffness with the decline of cognitive performance provides a framework for the investigation into the effects of yoga and its influence on cognitive function [47–49]. Whilst there are few studies which assess the effect of yoga on neuro-cognition, considering its capacity to improve a wide range of cardiovascular parameters, there may be corresponding improvements in the cognitive profile. Preliminary evidence in a study by Cohen et al. [50] demonstrates a strong association between the executive abilities of focused attention, processing speed, maintenance of effort, and QoL improvements after a yoga intervention in CR patients [50]. Whilst there is a significant body of evidence to support its use in healthy, psychosocially affected and various pathological populations, there are relatively few studies that examine a combination of psychosocial, cardiovascular, and cognitive effects in cardiac or CR populations. Given the impact of yoga across a broad range of health adaptations in various populations, we hypothesise that yoga will improve anxiety, depression and stress accompanied by improvements in cardiovascular parameters of HRV, PWV, CIMT, biomarkers and cognitive function in post-CR patients.

## Method and design

### Study design

This is a two arm, multi-centre, parallel-arm randomised controlled trial that will compare the outcomes of patients with cardiovascular disease assigned to a 12 week yoga intervention or to a no-treatment control group. The study will be conducted in approximately 134 post-CR participants over a period of 16 weeks comprising of a 12 week intervention period and 4 week follow up assessment. The primary outcome of this study is the component and overall scores obtained through the Depression Anxiety Stress Subscale (DASS) [51]. Secondary outcomes include QoL and cardiovascular and cognitive function. Timepoints for assessments will take place at baseline (week 0), mid-intervention (week 6), post-intervention (week 12), and at follow up (week 16). Ethics approval has been sought from the University of Western Sydney (H9402), Sydney Adventist Hospital Group (2011.40) and Western Sydney Local Health District Human Research Ethics Committees (2013/6/4.5(3747)).

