### Sample size and power calculation

To our knowledge, there is at present only one study which examines the effect of yoga training in post-CR patients [52]. This study assessed the effects of a 6 week yoga program on lipid profiles and brachial artery vasodilation in 10 post-CR patients and 23 healthy individuals however published data was insufficient to conduct a preliminary power analysis [52]. Given the DASS is a primary outcome measure in this study, a power analysis was conducted upon the results published in a meta-analysis on yogic effects in depression [34]. Results published by Cramer et al. [34] noted a standardised mean difference of 0.69 compared to usual care across five studies. Application of these findings as a basis for an approximated power calculation resulted in an estimated required sample size of 112 participants. Allowing a 20% drop-out rate, a total of 134 patients will be recruited in the current study. This power calculation has been conducted based on a population other than post-cardiac rehabilitation due to a lack of available data in this patient cohort to permit a more robust calculation. As such, an interim sample size analysis will also be conducted at n = 50 allowing for an acceptable estimate of the population standard deviation and hence considerably more robust sample size calculation to ensure adequate power.

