### Psychological outcomes

#### Depression Anxiety Stress Scales (DASS)

The DASS is a set of three self-reported scales designed to assess the negative emotional states of depression, anxiety and stress. Each of the three DASS sub-scales contains 14 items, divided into subscales of 2–5 items with similar content. The DASS has been employed in a number of studies in cardiac populations and has been shown to have good test-retest reliability coefficients for all scales [53]. The DASS scale was found to show better discrimination when assessed in comparison to a well-established coronary prone behavioural pattern scale such as the Framingham Scale in a group of Myocardial Infarction (MI) and matched control patients [54]. While not as widely used as other questionnaires of anxiety and depression such as the State Trait Anxiety Inventory, Beck Depression Inventory or Beck Anxiety Inventory, the DASS shows greater discriminant validity in regards to these psychosocial factors [11]. Participants will be asked to use 4-point severity/frequency scales to rate the extent to which they have experienced each state over the past week. Overall DASS scores will be calculated and presented for statistical analysis.

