### Statistical analysis

Analysis is to be performed using the R statistics package (version 3.1.1). All data will be inspected visually and statistically for normality (skewness and kurtosis between -1 and +1). Analysis of variance (ANOVA) and chi-squared tests of independence will be used to check for any differences between groups at study entry, any differences found here will be controlled for in that outcome analysis. Outcome analysis will take the form of ANCOVAs to detect changes between the experimental and control groups at post- treatment while controlling for baseline values and other possible confounders such as age, gender, time since cardiac incident, time since phase-2 CR completion and current exercise regimen or phase-3 CR participation. Multiple imputations will be used to impute missing data for participants with less than 10% missing data. An intention to treat analysis in which all missing data will be managed with multiple imputations will be conducted along with a separate per protocol analysis in which those with greater than 10% missing data or less than 60% yoga session attendance will be excluded. A p-value of less than 0.05 will be considered statistically significant.

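### The primary DASS outcome is defined as one, three or four scores in different sections, and a single unadjusted 0.05 threshold leaves the error rate of the main claim unfixed

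*Protocol article*

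**What the plan says.** All places are in the Protocol article.

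- **Abstract, Method and design:** "The primary outcomes of this study are negative affective states of anxiety, depression and stress assessed using the Depression Anxiety Stress Scale". This is three scores, with no overall score.
- **Study design:** "The primary outcome of this study is the component and overall scores obtained through the Depression Anxiety Stress Subscale (DASS"). Three components plus an overall score make four.
- **Depression Anxiety Stress Scales (DASS):** "Overall DASS scores will be calculated and presented for statistical analysis". Component scores are not mentioned as going to analysis.
- **Sample size and power calculation:** "Given the DASS is a primary outcome measure in this study, a power analysis was conducted". The score is not named. The effect comes from a meta-analysis on depression, which "noted a standardised mean difference of 0.69 compared to usual care across five studies". The section also plans to recalculate the sample size at n = 50 from an estimated standard deviation, without saying of which score.
- **Statistical analysis:** "Outcome analysis will take the form of ANCOVAs to detect changes between the experimental and control groups at post- treatment", and "A p-value of less than 0.05 will be considered statistically significant". No order of testing, division of alpha or rule for a positive primary result is given.

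**The concern.** A reader cannot tell whether the main claim rests on one, three or four tests. Each count has support somewhere in the document, so the score that carries the headline could be chosen after the data are seen, and the choice could be defended from the text. If one significant score among several is enough, the chance of declaring an effect when there is none exceeds 5%.

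The ambiguity also affects conduct. The recalculation at n = 50 needs the standard deviation of a particular score. A subscale and a total built from three subscales will in general have different standard deviations, so this step is not defined until the primary score is named.

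**Working it through.** **Step 1. Reproduce the planned sample size.** Inputs from the sample size section: SMD 0.69 and 112 participants before dropout. Not stated, so assumed: two-sided 0.05, 1:1 allocation, and the power.

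Normal approximation per arm: n = 2(z₀.₉₇₅ + z_power)² / 0.69².

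| Power | Total, normal approximation | Total, t-test |
|---|---|---|
| 80% | 66 | 68 |
| 90% | 90 | 92 |
| 95% | 110 | 112 |

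For 95%: 2(1.960 + 1.645)² / 0.4761 = 54.6, so 55 per arm. The t-test solution is 55.57, so 56 per arm and 112 in total. The stated 112 is therefore matched by one test at the full 0.05 with 95% power. One-sided versions at 80% to 95% power give totals of 52 to 94 and do not match.

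**Step 2. False-positive rate if any one score suffices.** Take three subscale test statistics Z₁, Z₂, Z₃ with common correlation r and no treatment effect. The overall score is their sum, with test statistic T = (Z₁ + Z₂ + Z₃) / √(3 + 6r). Each is tested two-sided at 0.05 (critical value 1.96).

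The document gives no value for r. The Background says only that for anxiety and depression "past attempts to quantify these constructs yielded high degrees of inter-correlation". A range of 0 to 0.9 is assumed. Results from 2,000,000 simulated draws per value:

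| r | Three subscales | Three subscales plus overall |
|---|---|---|
| 0 | 14.3% | 16.1% |
| 0.5 | 12.5% | 12.9% |
| 0.6 | 11.8% | 12.1% |
| 0.7 | 10.9% | 11.1% |
| 0.8 | 9.9% | just under 10% |
| 0.9 | 8.4% | 8.4% |

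Check at r = 0 for three scores: 1 − 0.95³ = 14.3%. Four independent tests would give 1 − 0.95⁴ = 18.5%, but that cannot occur here because the overall score is the sum of the other three.

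These figures count errors in either direction. Counting only false findings in favour of yoga, the four-score rate is 8.2% at r = 0, 6.5% at r = 0.5 and 4.2% at r = 0.9, against a nominal 2.5%.

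**Step 3. Cost of control.** With 56 per arm and SMD 0.69 assumed for every score (t-test):

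- alpha 0.05: power 95.1%
- alpha 0.05/3 = 0.0167: power 88.7%
- alpha 0.05/4 = 0.0125: power 86.5%

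With Bonferroni over four scores, the simulated family-wise rate is 4.4% at r = 0, 3.6% at r = 0.5 and 2.3% at r = 0.9.

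**The case against.** Several counter-arguments carry weight.

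- **The 5% is a per-test threshold.** The Statistical analysis section makes no trial-wise claim, and the rule that any one score suffices is inferred from silence. A rule that every score must be significant would need no adjustment. This stands: the inflated rates are conditional.
- **Multiplicity procedures are often left to an analysis plan.** None is shown and this is a condensed article, so the lack of a named procedure is not in itself the fault. The conflicting definitions of the primary outcome are, because a separate plan does not remove a contradiction printed here.
- **The DASS section may mean something else.** It describes three scales, each split into small item groups, and then speaks of overall scores in the plural. That can mean the total of each scale, which would agree with the abstract. It would still not agree plainly with the Study design section, which lists component and overall scores side by side.
- **A reader might infer that the error rate is at least doubled.** The document does not support that as a floor. The rate falls below 10% once r reaches about 0.8, and the Background's remark on high inter-correlation, though it concerns past measures, points towards that end.
- **A reader might also count weeks 6 and 16 as further primary tests.** The outcome ANCOVA is placed at post-treatment, so assessment at those visits does not make them primary tests.

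**Conclusion.** The point holds as a contradiction with a conditional consequence. The abstract, the Study design section and the DASS section do not define the same primary outcome, the sample size is built for one depression effect, and one unadjusted threshold applies to whatever is tested at week 12.

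If any one of the four scores may carry the claim, the false-positive rate is about 8% to 16% for correlations from 0.9 down to 0, and about 11% to 13% for 0.5 to 0.7. The three-score reading gives nearly the same (8.4% to 14.3%). With one primary score the rate is 5%.

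The figures assume two-sided tests and equal correlation between subscales. The relevant correlation is the one left after the ANCOVA adjustment, which the document does not give either. The contradiction itself rests on no assumption, and it should be corrected because it decides what the trial may conclude.

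**What to change.** Choose one of two routes and use the same wording in the abstract, Study design, Sample size and DASS sections.

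1. **One primary score.** Name one DASS score at week 12, tested two-sided at 0.05, and make the other DASS scores secondary. Which score to name is the sponsor's choice: the hypothesis lists the three states separately, the sample size rests on depression, and the document gives no effect size for the overall score.
2. **Several primary scores.** Keep the three subscales, or all four scores, and test them with Holm at a family-wise 0.05. State that success on any one supports a claim for that score only.

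In either case, state which score's standard deviation feeds the recalculation at n = 50.

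**Cost.** Route 1 is a change of wording and needs no division of alpha. For route 2, per-test power with Bonferroni falls from about 95% to about 89% for three scores or 86% for four, and Holm does no worse. The 95% is back-calculated, as the protocol states no power, and all these figures assume 56 analysed per arm and SMD 0.69 for every score.

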### Sample size and power calculation

To our knowledge, there is at present only one study which examines the effect of yoga training in post-CR patients [52]. This study assessed the effects of a 6 week yoga program on lipid profiles and brachial artery vasodilation in 10 post-CR patients and 23 healthy individuals however published data was insufficient to conduct a preliminary power analysis [52]. Given the DASS is a primary outcome measure in this study, a power analysis was conducted upon the results published in a meta-analysis on yogic effects in depression [34]. Results published by Cramer et al. [34] noted a standardised mean difference of 0.69 compared to usual care across five studies. Application of these findings as a basis for an approximated power calculation resulted in an estimated required sample size of 112 participants. Allowing a 20% drop-out rate, a total of 134 patients will be recruited in the current study. This power calculation has been conducted based on a population other than post-cardiac rehabilitation due to a lack of available data in this patient cohort to permit a more robust calculation. As such, an interim sample size analysis will also be conducted at n = 50 allowing for an acceptable estimate of the population standard deviation and hence considerably more robust sample size calculation to ensure adequate power.

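### 134 recruits with 20% drop-out leave 107 participants, not the required 112, because 112 was multiplied by 1.2 instead of divided by 0.8

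*Protocol article*

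**What the plan says.** The section on sample size and power takes its effect size from a meta-analysis of yoga in depression, which "noted a standardised mean difference of 0.69 compared to usual care across five studies". Applying that effect "resulted in an estimated required sample size of 112 participants". The next sentence makes the allowance for losses: "Allowing a 20% drop-out rate, a total of 134 patients will be recruited in the current study". The Study design section repeats the total: "The study will be conducted in approximately 134 post-CR participants".

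The sample size section also says that the calculation borrows from a different population, and that "an interim sample size analysis will also be conducted at n = 50" to obtain a better estimate of the standard deviation. It does not state the power, the sidedness of the test or the allocation ratio.

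**The concern.** A drop-out rate is a proportion of those who enter the trial. To finish with a given number, that number is divided by one minus the rate. Here the required number appears to have been increased by 20% instead, which always gives a smaller total: 1.2 × 0.8 = 0.96, so the completers come out 4% below the requirement whatever the starting size.

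Two things are at stake. First, the recruitment total is a headline design figure that appears in two sections, and it does not deliver what the protocol says it delivers. Second, readers and those who monitor the trial will judge attrition against a stated tolerance of 20%, when the total tolerates only about 16% before falling below the stated requirement.

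**Working it through.** **Inputs from the protocol.** Required size 112, drop-out rate 20%, recruitment total 134 and standardised mean difference (SMD) 0.69, all from the sample size section. Two parallel arms, from Study design. Significance threshold 0.05, from Statistical analysis.

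**Assumptions, because the protocol does not state them.** Two-sided test and 1:1 allocation. These matter only for the power figures in steps 4 to 6, not for the drop-out arithmetic.

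1. *Reproduce the stated total.* 112 × (1 + 0.20) = 134.4, which rounds to the stated 134. The usual formula, 112 / (1 − 0.20) = 140, does not give 134; the difference is 6 recruits.

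2. *Apply the stated drop-out to the stated total.* 134 × (1 − 0.20) = 107.2, so about 107 remain. The shortfall against 112 is 112 − 107.2 = 4.8, or about 5 participants (4.8 / 112 = 4.3%).

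3. *Find the drop-out that 134 does cover.* (134 − 112) / 134 = 22 / 134 = 16.4%.

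4. *Check where 112 comes from.* For a two-sample t-test at SMD 0.69 and two-sided 0.05, the totals with equal arms are:

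| Assumed power | Solved total | Rounded up to equal arms |
|---|---|---|
| 80% | 67.9 | 68 |
| 90% | 90.2 | 92 |
| 95% | 111.1 | 112 |

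Of these conventional levels, only 95% gives 112. This supports reading 112 as the number needed for analysis, before any allowance for losses.

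5. *Effect on power at the cited SMD.* With 112 (56 per arm), power is 95.1%. With 107 (53.5 per arm), it is 94.2%. The loss is about one percentage point.

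6. *Sensitivity to the unstated power.* Suppose 112 had been sized for 80% or 90% power instead. The effect it could detect would then be an SMD of 0.534 or 0.618, and 107.2 completers (53.6 per arm) would give 78.2% or 88.7% power. The loss is then about 1 to 2 points.

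**The case against.** The strongest reply does not dispute the arithmetic; it says that the slip hardly matters. It has four parts.

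- *Power is barely touched.* About 107 completers still exceed the totals for 80% power (68) and 90% power (92) at the cited SMD. This stands: the trial is not underpowered at that effect on account of this error. The 95% behind 112 is also inferred rather than documented.

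- *The target is provisional.* The protocol admits that the calculation is approximate and plans to revisit the size at n = 50, and Study design says only approximately 134. This is true, and a gap of 6 recruits is small beside the uncertainty in an effect borrowed from another population. But that review is planned in order to re-estimate the standard deviation. It does not correct the inflation step, and the same step applied to a new requirement would again fall 4% short.

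- *The intention-to-treat analysis keeps everyone.* The Statistical analysis section plans multiple imputation of all missing data, so drop-outs stay in that analysis. This softens the loss, but imputation does not recover all the missing information. The protocol itself chose to inflate for drop-out, and so treats 112 as the number needed after losses. The separate per protocol analysis excludes people for missing data or low attendance, so losses count directly there.

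- *Baseline adjustment buys precision.* If 112 came from an unadjusted comparison (an assumption), a baseline-to-outcome correlation r with 1 − r² = 107 / 112 = 0.955, that is r of about 0.21, would offset the shortfall. This is plausible, but the protocol does not claim it as the basis for the size.

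These points limit the consequence. None of them makes 134 agree with 112 after 20% drop-out.

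**Conclusion.** The concern holds. The required size, the drop-out rate and the recruitment total are mutually inconsistent as written: at 20% drop-out, 134 leaves about 107, not 112, and keeping 112 takes 140. This conclusion rests only on the three stated figures and on the ordinary meaning of a drop-out rate.

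The error is certain but small: 6 recruits, about 5 completers, and roughly one percentage point of power at SMD 0.69. The power statement assumes a two-sided 0.05 t-test with equal arms. It is a figure to correct, not a reason to doubt that the trial can detect the effect it cites.

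**What to change.** Change the drop-out sentence in the sample size section in one of these ways:

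- keep 134 and state that it allows for about 16% drop-out, leaving 112; or
- keep 134 and 20%, and state that about 107 participants are then expected to remain. If a power figure is added (about 94% at SMD 0.69), give with it the two-sided 0.05 test and 1:1 allocation that it assumes, once the trial team confirms that these match its design; or
- keep both 112 and 20%, and raise the recruitment total to 140 here and in Study design.

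The first two options change wording only and need no extra enrolment; the price is a slightly less favourable stated allowance. The third needs 6 more recruits. Whichever is chosen, the sample size review at n = 50 should divide the new requirement by one minus the drop-out rate, so that the 4% shortfall is not carried into the revised target.
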